### **SAFETY ISSUES**

An expert panel of a WHO Informal Consultation in 2002 recommended that deworming, and specifically the usual dose of mebendazole (500mg), could be safely given to children 12 to 24 months of age. In older age groups, side-effects are infrequent and, if present, are only mild and transient. Therefore, negligible risks are anticipated to be associated with deworming in this study. There is some concern that deworming pills could pose a choking hazard to younger children; however, the pills in this trial will be crushed and mixed with a fruit purée to eliminate this risk. The ascertainment of health and nutrition outcomes, including measurement of weight and length, carry no risk and will be conducted by the research team in a similar manner as is routinely conducted in early childhood health services.

### **ANTICIPATED BENEFITS**

Currently, routine deworming of preschool-age children is not conducted in Peru. Children participating in the study will benefit directly by receiving deworming treatment at least once during the course of the study. Parents will also receive the laboratory results of the stool examinations upon completion of the study. The results of the study will inform health services in Peru and in other countries in providing deworming programs to preschool-age children.

### **POTENTIAL RISKS**

There are no foreseeable risks associated with participation in this study. The deworming tablet, mebendazole, is very safe and effective and is being given to preschool-age children in many parts of the world. Most children do not have any side effects at all after deworming. If symptoms do occur, they are minor and temporary and usually disappear within 48 hours. PAHO and the World Health Organization consider mebendazole very safe and in fact recommend that it be given to preschool-age children where parasites are common.

### **PRIVACY AND CONFIDENTIALITY**

Children will be assigned an identification number for the duration of the study to ensure the confidentiality of the results. All original documents, including questionnaires and informed consent forms, will be kept in a locked cabinet and room. Preserved stool specimens will be marked with the assigned identification number and kept in a locked refrigerator. All electronic information, such as databases, will be stored on a password-protected computer in a locked room. Access to original documents, electronic information and preserved stool specimens will be restricted to the Project Director, Principal Investigator and study coordinator only.

### **ETHICAL OVERSIGHT**

The principal investigator, co-investigators and all other research personnel will conduct the study in an ethical manner which is consistent with the international principles of good research practice and will function according to institutional policies of the McGill University Health Centre and the Asociación Civil Selva Amazónica, governing human subject research and all applicable research guidelines. Ethics approval will be obtained and maintained from the Research Ethics Board in Canada and the National Institute of Health, the Ministry of Health, and the Instituto de Investigación Nutricional in Peru. The trial will be registered according to international regulations. The integrity of the trial with respect to blinding will be ensured in the following way: only one member of the research team will be unblinded to prepare the selected stool specimens for examination (i.e. that group that will be treated at either the 12 or 18-month time point). All other persons on the research team will remain blinded. Results of stool examinations will be available to mothers at the end of the study. Mothers of participating children will be properly informed of their rights as study subjects and informed consent will be obtained prior to randomization.

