Stool specimens will be collected from all children to assess the prevalence and intensity of STH infections. All stool specimens will be transferred to the laboratory at the local research office (the Asociación Civil Selva Amazónica); however, at the 12-month visit, only specimens from children receiving deworming treatment will be examined for the presence and intensity of STH infection (e.g. *Ascaris*, *Trichuris* and hookworm). At the 18-month CREDE visit, only stool specimens from children receiving deworming treatment will be analyzed. One member of the research team will be unblinded to treatment status to arrange for the appropriate specimens to be

analyzed. (All other research personnel will remain blinded to maintain the double-blinding of the trial). This approach to examining stool specimens from identified treatment groups is required so that children found infected will be treated, thus meeting the ethical requirement to treat children who are known to be infected (based on a positive stool specimen). This approach also ensures that a baseline (at 12 months) and interim (at 18 months) estimate of worm prevalence, and worm intensity (which requires a fresh stool specimen) is obtained. These specimens which are to be analyzed immediately will be examined by a trained microscopist using the Kato-Katz method. This is the recommended technique for assessment of the prevalence and intensity (eggs per gram) of intestinal parasitic infection in fresh stool . For a one-stool specimen, sensitivity and specificity are over 96% for *Ascaris* and over 91% for *Trichuris* . There is lower sensitivity and specificity for hookworm; however, hookworm infection prevalence is negligible in this age group, so this should not bias the results.

Stool specimens from children receiving usual care and placebo at 12 and/or 18 months will be preserved in sodium acetate-acetic acid-formalin (SAF) and analyzed upon completion of the study using the ether-concentration method, the recommended technique for estimating worm prevalence from preserved samples.

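### Stool tubes stored only for placebo visits, under the study ID and open to three roles, make allocation deducible by more than the one person declared unblinded

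*Protocol*

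**What the plan says.** **The blinding claim.** Ethical oversight states that "only one member of the research team will be unblinded to prepare the selected stool specimens for examination". Outcome measurements makes the same promise about everyone else: "All other research personnel will remain blinded to maintain the double-blinding of the trial".

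**How stool is handled.** Outcome measurements ties handling to the treatment given. For the first visit, "at the 12-month visit, only specimens from children receiving deworming treatment will be examined for the presence and intensity of STH infection". For the second, "At the 18-month CREDE visit, only stool specimens from children receiving deworming treatment will be analyzed". On the reading itself, "These specimens which are to be analyzed immediately will be examined by a trained microscopist using the Kato-Katz method". Stool from a child given placebo at either visit is fixed in SAF and read after the study ends. At 24 months all four groups are read fresh. The stated reason for the split is ethical: no child should be known to be infected and left untreated.

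**Labels and access.** Privacy and confidentiality gives each child one identification number for the whole study. It then says: "Preserved stool specimens will be marked with the assigned identification number and kept in a locked refrigerator". On custody: "Access to original documents, electronic information and preserved stool specimens will be restricted to the Project Director, Principal Investigator and study coordinator only".

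**Laboratory quality control.** Quality control during fieldwork has the laboratory supervisor re-read 10% of each microscopist's slides, masked to the first result. It does not mention masking to treatment.

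**The concern.** The rule that decides whether a specimen is preserved is the child's treatment at that visit. A stored tube from 12 or 18 months is therefore, by definition, a placebo tube. Once it bears the study ID and can be seen by people with access to the trial data, it works as a partial unblinding list. That cannot be squared with a promise that one person alone is unblinded.

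A related signal reaches the laboratory. Any slide presented fresh at 12 or 18 months must come from a child dewormed at that visit.

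Two things are at stake. First, the Protocol's background section faults earlier trials for weak concealment and blinding, and this trial offers its double-blind design as the remedy. Second, worm prevalence and intensity at 24 months are secondary outcomes that depend on a person counting eggs. They are the outcomes most open to influence if a reader knew a child's earlier treatment.

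**Working it through.** The point is logical, not numerical, and the Protocol gives no figure to reproduce. The check is whether specimen handling identifies the group, and for whom.

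**Inputs**
- Treatment by group and visit: Intervention groups.
- Fresh reading after mebendazole, preservation after placebo, at 12 and 18 months: Outcome measurements.
- Study ID on preserved tubes, and three roles with access: Privacy and confidentiality.
- 440 children per group, 1,760 in all, 20% attrition over 12 months: Sample size.

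**Step 1: handling by group**

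| Group | 12 months | 18 months | Handling pattern |
|---|---|---|---|
| 1 | mebendazole | placebo | fresh, preserved |
| 2 | placebo | mebendazole | preserved, fresh |
| 3 | mebendazole | mebendazole | fresh, fresh |
| 4 | placebo | placebo | preserved, preserved |

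Four groups give four different patterns, so the mapping is one-to-one. One visit alone separates Groups 1 and 3 from 2 and 4 (at 12 months), or Groups 2 and 3 from 1 and 4 (at 18 months).

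**Step 2: what the refrigerator shows**
- A tube from a visit proves placebo at that visit.
- Tubes from both visits prove Group 4.
- A tube from one visit only points to Group 2 (12 months) or Group 1 (18 months), provided a specimen was given at the other visit.
- No tube at all points to Group 3, but also fits a child who gave no specimen.

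The fresh-reading records would settle the doubtful cases. The same three roles have access to electronic information.

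**Step 3: how many tubes**
- Preserved at 12 months: Groups 2 and 4, 2 × 440 = 880.
- Preserved at 18 months: Groups 1 and 4, 2 × 440 = 880 with no losses. If the whole 20% attrition fell before 18 months, 880 × 0.8 = 704.

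These are ceilings, and every missing specimen lowers them.

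**Step 4: how many people**
- Declared unblinded: 1.
- Roles with access to the tubes and the data: 3.
- If the declared member is one of the three, 3 − 1 = 2 others can deduce allocation; if not, all 3 can. Hence at least two, taking the roles to be held by different people.

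**Step 5: the laboratory**
- Stated facts are enough for a reader, or the supervisor on re-reading, to infer treatment at that visit for a slide read fresh at 12 or 18 months.
- Carrying this to a 24-month slide needs two further conditions: fresh specimens bear the study ID, and the same staff read at 24 months. The ID label is stated only for preserved tubes, and the 24-month readers are not identified.

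**The case against.** The access rule is a confidentiality measure that narrows who may see the material. It does not describe anyone comparing refrigerator contents across visits. That stands: the text shows that allocation can be deduced, not that anyone would deduce it. It does not remove the contradiction, because a blinding claim rests on people being unable to know.

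The placebo is matched to the active tablet, and the primary outcome is duplicate weight on an electronic scale calibrated daily. The nurses who give the tablets, weigh and measure the children and assess development do not appear on the access list and are not the slide readers. This stands in full and limits the reach of the point.

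Three stronger readings are tempting, and the Protocol does not support them:

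- *Microscopists know every child's group.* That would need the study ID on fresh slides, linkage of readings six months apart across several microscopists, and a way to tell a preserved specimen from one never given. None of these is stated.
- *Readers who know past treatment judge the 24-month slides.* This is plausible, but the Protocol does not say who reads them.
- *The three roles could steer data cleaning or the adjustment that is made only if needed.* Primary analysis assigns that adjustment to no one, and the text at hand does not assign data cleaning to these roles.

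**Conclusion.** The point holds as a contradiction within the Protocol. Outcome measurements and Ethical oversight declare one unblinded person. The handling rule, together with the labelling and access rules in Privacy and confidentiality, puts at least two more in a position to deduce allocation, from at most about 880 placebo tubes per visit. It rests on the three roles being different people and on stored tubes being identifiable by visit, which their later analysis requires.

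For laboratory staff, the supported conclusion is limited to treatment at the visit in question for slides read fresh. The risk is mainly to the secondary 24-month prevalence and intensity outcomes, and there it depends on the two unstated conditions in Step 5. A reader might infer that the double-blind design fails as a whole; that does not follow, since weight, length and development are measured by staff not exposed by this route. The change is worth making because the Protocol itself sets the conflicting rules and the repair is simple.

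**What to change.** Reconcile Outcome measurements, Privacy and confidentiality, and Ethical oversight with two changes:

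1. Label all stool specimens, fresh and preserved, at all three visits with a random laboratory code in place of the study ID. Issue a new code at each visit, so that a reader cannot link a 24-month slide to an earlier one. Only the one unblinded member holds the link list.
2. Amend Privacy and confidentiality so that this member, and not the three listed roles, holds the preserved specimens and the 12- and 18-month stool logs and results until database lock. The results must be covered too, because during the trial they would exist only for children dewormed at that visit.

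The rule that stool from children given placebo goes unread until the study ends is untouched, and mothers can still receive results then. Readers will still know that a slide read fresh at 12 or 18 months comes from a child treated at that visit, but the code stops that knowledge from travelling to 24 months.

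**Cost.** Relabelling covers up to 1,760 × 3 = 5,280 specimens, leaving aside the post-treatment efficacy samples. One person carries the linkage, and custody changes hands. Preserving an aliquot from every child, so that a stored tube no longer signals placebo, is optional. It would add up to 880 tubes per visit and is not needed once the two changes are in place.

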### **COMPENSATION**

There are no costs associated with participation in this study as visits will take place during

routine health centre visits according to the Peruvian Ministry of Health schedule. Study treatments and testing of stool specimens will be free of charge for the duration of the study. The cost of travel for the follow-up visits at the 18- and 24-month CREDE visit will be reimbursed to encourage participation and follow-up during the course of the study.

### **RESULT DISSEMINATION**

The results of this trial will be published and presented in national and international fora, including scientific conferences and peer-reviewed journals. Presentations will also be made at the Pan American Health Organization (PAHO), WHO and in appropriate local, regional and national fora in Peru. The results will be of interest to all 130 STH-endemic countries that are currently, or that are planning to, implement deworming interventions in preschool-age populations. The results will be sent to newsletters such as Action Against Worms and to global initiatives such as Deworm the World, Children without Worms, the Mebendazole Advisory Committee, Partners for Parasite Control and Partnership for Child Development, among others.

### **FUNDING**

This study is supported by a grant from the Thrasher Research Fund ([name]). The duration of funding is three years, commencing on February 1, 2011.

### **TIMELINE OF RESEARCH ACTIVITIES**

Table 1. Timeline of proposed activities for the randomized-controlled trial of deworming of 12 to 24 month old infants in the Peruvian Amazon.

| ACTIVITIES                             | 2010                    |                         | 2011                    |                         |                         |                         | 2012                    |                         |                         |                         | 2013                    |                         |
|----------------------------------------|-------------------------|-------------------------|-------------------------|-------------------------|-------------------------|-------------------------|-------------------------|-------------------------|-------------------------|-------------------------|-------------------------|-------------------------|
|                                        | 3 rd Quarter | 4 th Quarter | 1 st Quarter | 2 nd Quarter | 3 rd Quarter | 4 th Quarter | 1 st Quarter | 2 nd Quarter | 3 rd Quarter | 4 th Quarter | 1 st Quarter | 2 nd Quarter |
| Ethics approval (Canada and Peru)      | ✓                       | ✓                       | ✓                       |                         |                         |                         |                         |                         |                         |                         |                         |                         |
| Purchase of study materials/supplies   | ✓                       | ✓                       | ✓                       |                         |                         |                         |                         |                         |                         |                         |                         |                         |
| Trial registration                     |                         | ✓                       |                         |                         |                         |                         |                         |                         |                         |                         |                         |                         |
| Preliminary visits to health centres   |                         |                         | ✓                       |                         |                         |                         |                         |                         |                         |                         |                         |                         |
| Pre-testing of the questionnaire       |                         |                         | ✓                       |                         |                         |                         |                         |                         |                         |                         |                         |                         |
| Training of the research nurses        |                         |                         | ✓                       | ✓                       |                         |                         |                         |                         |                         |                         |                         |                         |
| Pre-recruitment period                 |                         |                         | ✓                       | ✓                       |                         |                         |                         |                         |                         |                         |                         |                         |
| Recruitment period                     |                         |                         |                         | ✓                       | ✓                       | ✓                       |                         |                         |                         |                         |                         |                         |
| 18-month follow-up visit               |                         |                         |                         |                         |                         | ✓                       | ✓                       | ✓                       |                         |                         |                         |                         |
| 24-month follow-up visit               |                         |                         |                         |                         |                         |                         |                         | ✓                       | ✓                       | ✓                       |                         |                         |
| Data analysis                          |                         |                         |                         |                         |                         |                         |                         |                         |                         | ✓                       | ✓                       |                         |
| Reporting (presentations, manuscripts) |                         |                         |                         |                         |                         |                         |                         |                         |                         | ✓                       | ✓                       |                         |
| Results dissemination                  |                         |                         |                         |                         |                         |                         |                         |                         |                         |                         |                         | ✓                       |

